## Abstract

*Introduction:* Several strategies have been devised to safely limit the use of thoracic imaging in patients suspected of pulmonary embolism (PE). However, they are based on different rules for clinical probability (CP) assessment, rendering their combination difficult. The four-level pulmonary embolism probability score (4PEPS) allows the combination of all other strategies using a single CP assessment. *Methods and analysis:* Pragmatic cluster-randomized trial in 20 EDs. Patients with suspected PE will be included and followed for 90 days (number of patients to be included: 2560, 1280 in each arm). Ten centers will be allocated to the control group where physicians will be free to do as they see fit but they will be given the recommendation to apply a validated strategy. Ten centers will be allocated to the interventional group where the physicians will be given the recommendation to apply the 4PEPS strategy. The primary objective will be to demonstrate that the application of the 4PEPS strategy by the emergency physicians, in comparison to current practices, (i) does not increase the risk of serious events related to diagnostic strategies and (ii) significantly reduces the use of thoracic imaging. *Ethics and dissemination:* The study will be submitted for approval to an institutional ethics review board for all participating centers. If successful, the SPEED&PEPS trial will have an important impact for patients suspected of PE limiting their irradiation and for public health in substantial savings in terms of the direct cost of diagnostic investigations and the indirect cost of hospitalizations due to waiting times or delayed harmful effects. *Funding:* This work is funded by a French Public Health grant (PREPS-N 2019). The funding source plays no role in the study design, data collection, analysis, interpretation or the writing of the manuscript. *Trial registration:* ongoing. *Trial status:* not started.

## 1. Introduction

The increased use of X-ray examinations in diagnostic approaches used at emergency departments is a major public healthcare issue in three ways: (i) for patients, due to the risks linked to cumulative radiation exposure and the resulting longer care time; (ii) for healthcare professionals, because it contributes to overcrowding in emergency departments; and (iii) for society as a whole due to the cost [1]. Suspected pulmonary embolism (PE) is without doubt one of the most striking examples [2]. Given that PE is a potentially life-threatening condition without any specific symptoms or clinical signs, it is often put forward as a possible diagnosis, which leads to ancillary investigations—mainly a D-dimer test and/or computed tomography pulmonary angiography (CTPA) [3,4,5]. In the last twenty years, the number of patients who undergo a CTPA to screen for PE has multiplied by ten while the PE prevalence among investigated patients has dropped from more than 25% to less than 5% [2]. At the same time, the incidence of PE increased but without significant impact on morbidity and mortality [6]. Indeed, PE-related mortality continues to decrease but to a lesser extent than before the wide spread of CTPA and to a much lesser extent than the rise in PE diagnosis [6]. This observation has highlighted another risk linked to the overuse of CTPA, namely overdiagnosis. The greater the use of CTPA, the greater the risk of false positives, especially when the quality of the CTPA is suboptimal. This is combined with the advances in CTPA’s abilities to show subsegmental PE which may not be of clinical relevance and lead to initiating unnecessary anticoagulant treatment [7].

Several strategies have therefore been devised to limit the use of CTPA, based on the formalized assessment of clinical probability (CP) and/or by modifying the cut-off value for D-dimer tests. Yet, each of these strategies is based on a different and specific method of assessing CP: the PERC (pulmonary embolism rule-out criteria) and implicit assessment for ruling out PE on clinical criteria [8,9,10], the YEARS rule or the adapted Wells score for ruling out PE on CP-adjusted D-dimer cut-off [11,12], and the revised Geneva score or the Wells score for ruling out PE on age-adjusted D-dimer cut-off [13,14]. This makes them difficult to use and combine, and can lead to non-expert physicians misusing these rules or relying solely on their empirical assessment, thereby exposing themselves to the risk of a misdiagnosis (loss of reliability) or inappropriate use of CT (loss of efficacy). 

We have developed and validated a score that combines all these possibilities into a single rule: 4PEPS (four-level pulmonary embolism probability score) [15]. Based on ISTH recommendations and depending on the prevalence of VTE in the population, the acceptable number of false negatives has been set to 2% [16]. Using 12 variables, 4PEPS defines four levels of CP that rule out a PE, namely (1) based only on clinical data (very low CP: PEPS < 0), (2) based on a D-dimer level < 1000 µg/L (low CP: PEPS ≥ 0 et < 5), (3) based on a D-dimer level with an age-adjusted cut-off value (moderate CP: PEPS ≥ 5 and <12), or (4) the diagnosis cannot reliably be ruled out based on a D-dimer test (high CP: PEPS ≥ 12) (Table 1). Assessed retrospectively based on large databases, the 4PEPS strategy seems to be more efficient and just as safe as the other strategies [15,17,18]. 

Our research hypothesis is that a diagnostic strategy based on 4PEPS will help reduce the use of thoracic imaging without increasing the risk of serious adverse events linked to the diagnostic approach. 

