### 3.2. Secondary Objective(s) and Endpoint(s)

The first secondary objective is to demonstrate that the risk of false-negative diagnosis with the 4PEPS strategy is very low in accordance with the ISTH criteria for validation of rule-out PE diagnostic strategies. The endpoint will be the false-negative rate defined as the rate of thromboembolic events occurring in the 90 days following inclusion in patients for whom PE was ruled out according to the 4PEPS strategy and who were not treated with anticoagulants. ISTH recommendations state the upper limit of the 95% confidence interval (95%CI) of this 90-day thromboembolic event rate should be less than 1.82 + 0.00528* prevalence, i.e., a rate ≤1.89% for a prevalence of 14% [16].

The second secondary objective is to demonstrate that the 4PEPS strategy (intervention group) is not inferior to current practices (control group) as regards the risk of false-negative diagnosis. The false-negative rate will be defined as the rate of thromboembolic events occurring in the 90 days following inclusion in patients for whom PE was ruled out and who were not treated with anticoagulants. 

The other secondary objectives are to evaluate and compare to usual practice the impact of the 4PEPS strategy as regards the rate of D-dimer measurement and the length of time spent in the emergency department by patients with suspected PE.

The ancillary objectives are to assess the rate of incidental findings on CTPA, the acceptance by physicians and their use in everyday practice of the clinical decision support tool SPEED [23], as regards the rate of patients for whom the SPEED application is used in real time (i.e., when the data that enable the automatic calculation of the clinical probability and the reminder of the appropriate diagnostic strategy have been entered before any additional examinations are performed, in particular, the D-dimer test); and to evaluate the appropriateness of diagnostic management according to international guidelines and if it differs when the SPEED application is used in real time or not. 

We will also evaluate and compare to usual practice the medico-economic impact of the 4PEPS strategy in terms of cost per serious clinical event related to the diagnostic procedure avoided in the 90 days following inclusion (cost–efficacy analysis). The endpoint will be the differential cost–efficacy ratio at 90 days.

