### 6.2. Strategy under Study: Interventional Group

Physicians of the participating centers in the intervention group will have the recommendation to apply the 4PEPS strategy. To make it easier to apply, the 4PEPS score will be included in SPEED [23]. Investigators will be asked to enter the information relating to patients included in the study directly into SPEED before performing any testing. Entering these data will enable the 4PEPS score to be calculated automatically and specific recommendations to be provided. A paper version of the CRF will also be available.

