## 9. Statistical Analysis

### 9.1. General Considerations 

Population characteristics will be described using their mean/standard deviation, median/interquartile range, or percent/95% confidence interval, as appropriate. Univariate comparisons will be made using Student’s, Mann–Whitney, or Fisher’s exact tests, as appropriate. The alpha risk will be set at 5%. All tests will be one-sided. Given that some proportions are expected to be small, confidence intervals will be calculated using the Clopper and Pearson exact method. 

The analysis will be performed using R software (R Foundation for Statistical Computing; 2008. http://www.R-project.org (accessed on 1 November 2022)) and its PropCIs and MASS add-ons (http://CRAN.R-project.org/package=PropCIs (accessed on 1 November 2022)). All objectives will be analyzed on the overall included population (intention-to-treat). A complementary per-protocol analysis will be performed, especially for the 4PEPS strategy in the interventional group. 

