### 9.3. Secondary Statistical Analysis

The confidence interval of the false-negative rate with the 4PEPS strategy will be calculated on an intention-to-treat basis and then on a per-protocol basis, and its upper limit will be compared with the limit considered acceptable by the ISTH recommendations based on the prevalence in the study: 1.82 + 0.00528* prevalence, i.e., for a prevalence of 14%, an upper limit ≤1.89% [16]. 

Hierarchical analysis of the other secondary outcomes will be conducted using a mixed effects logistic regression. If the primary safety endpoint and then the primary efficacy endpoint are confirmed, the false-negative rate with the 4PEPS strategy will be compared to that of the usual approaches in the control group using a mixed-effects logistic regression with a non-inferiority limit set at 1.35% [27]. If this endpoint is confirmed, then the two other secondary endpoints will be analyzed using the Holm procedure for multiple testing correction.

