## Figures and Tables

**Table 1 diagnostics-12-03101-t001:** 4PEPS or 4-Level Pulmonary Embolism Clinical Probability Score.

Field	Criterion	Points
Demographic data	Age < 50 years old	−2
	Age ≥ 50 years old and <65 years old	−1
	Male	+2
Medical history	Chronic pulmonary disease	−1
	Personal history of VTE	+2
	Hormonal estrogenic treatment	+2
	Immobility within the last 4 weeks ^a^	+2
Signs and symptoms	Heart rate < 80 beats per minute	−1
	Combination of chest pain and acute dyspnea	+1
	Syncope	+2
	Pulse oxygen saturation (SpO2) < 95%	+3
	Calf pain and/or unilateral lower limb edema	+3
Differential diagnosis	PE is the most likely diagnosis	+5
Categories of clinical probability	Very low CP: PE can be ruled out	<0
	Low CP: PE can be ruled out if D-dimer < 1000 µg/L	0 to 5
	Moderate CP: PE can be ruled out if D-dimer < 500 μg/L or <(age × 10) μg/L	6 to 12
	High CP: PE cannot be ruled out without imaging testing	>12

^a^ Surgery (under general anesthesia), lower-limb plaster cast or bedridden > 3 days for acute medical condition within the last 4 weeks.

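### The Introduction and Table 1 give different 4PEPS category boundaries, so scores of exactly 5 and exactly 12 carry two conflicting management rules

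*Protocol article*

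**What the plan says.** The protocol article states the category boundaries of the score twice.

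- **Section 1 (Introduction):** very low is below 0; low is 0 to below 5, with exclusion at a D-dimer below 1000 µg/L; the next level is "moderate CP: PEPS ≥ 5 and <12", with exclusion on an age-adjusted D-dimer cut-off; at the top level "the diagnosis cannot reliably be ruled out based on a D-dimer test (high CP: PEPS ≥ 12". The sentence refers the reader to Table 1.
- **Table 1 (Figures and Tables):** very low is below 0. The row "Low CP: PE can be ruled out if D-dimer < 1000" µg/L covers 0 to 5. The moderate row covers 6 to 12, with exclusion below 500 µg/L or below age × 10 µg/L. The row "High CP: PE cannot be ruled out without imaging testing" covers scores above 12.

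Three other places rely on the rule without restating its boundaries. Section 6.2 says of the SPEED software: "Entering these data will enable the 4PEPS score to be calculated automatically and specific recommendations to be provided". Section 3.2 defines the first secondary endpoint "in patients for whom PE was ruled out according to the 4PEPS strategy", and section 9.3 adds that "its upper limit will be compared with the limit considered acceptable by the ISTH recommendations". Section 9.1 states: "A complementary per-protocol analysis will be performed, especially for the 4PEPS strategy in the interventional group".

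**The concern.** The boundaries are the decision thresholds of the intervention. A patient scoring exactly 5 or exactly 12 falls in one category under the text and in the next lower one under the table, and the permitted use of D-dimer differs between the two. No other section says which set applies.

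The consequences are most direct where an analysis depends on the rule itself. The 4PEPS false-negative rate needs to know who was ruled out by the strategy, and the per-protocol analysis needs to know who was managed in line with it. The same patient could be adherent under one set and a deviation under the other. The boundaries also fix the recommendation issued to physicians in the intervention centers. Both primary endpoints are counted in all included patients by randomized center, so they are affected only indirectly, through that recommendation.

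**Working it through.** **Inputs.** The boundaries come from section 1 and Table 1; the item points and the D-dimer limits come from Table 1. The Introduction does not spell out its age-adjusted cut-off, so I take it to be the one in Table 1, that is, the larger of 500 and 10 × age (µg/L).

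**1. The two rules side by side, for a whole-number score**

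| Category | Introduction | Table 1 |
|---|---|---|
| Very low | below 0 | below 0 |
| Low | 0 to 4 | 0 to 5 |
| Moderate | 5 to 11 | 6 to 12 |
| High | 12 or more | 13 or more |

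Each column covers every score once, with no gap or overlap. They differ only at 5 (moderate against low) and at 12 (high against moderate).

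**2. Can these scores occur?** With 3 age levels and 11 yes/no items there are 3 × 2^11 = 6144 combinations. Enumerating them gives whole-number scores from −4 to 22. A score of 5 arises in 384 combinations and 12 in 455. These are unweighted counts of combinations, not shares of patients; they show only that both scores are attainable. Plain examples:

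- Score 5: a woman aged 65 or over, heart rate 80 or more, whose only positive item is PE as the most likely diagnosis (+5).
- Score 5: a man (+2) aged 65 or over, heart rate 80 or more, with SpO2 below 95% (+3); 2 + 3 = 5.
- Score 12: the same man with PE as the most likely diagnosis (+5) and recent immobility (+2); 2 + 3 + 5 + 2 = 12.

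**3. What changes at score 5.** The text excludes PE below max(500, 10 × age); Table 1 excludes it below 1000. Management differs only for a D-dimer between these limits, a window of width 1000 − max(500, 10 × age):

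| Age | Age-adjusted limit (µg/L) | Disputed D-dimer range (µg/L) | Width |
|---|---|---|---|
| 50 or under | 500 | 500 to <1000 | 500 |
| 60 | 600 | 600 to <1000 | 400 |
| 70 | 700 | 700 to <1000 | 300 |
| 80 | 800 | 800 to <1000 | 200 |
| 90 | 900 | 900 to <1000 | 100 |
| 100 | 1000 | none | 0 |

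For example, a 60-year-old with score 5 and a D-dimer of 800 µg/L is not excluded under the text (800 is above 600) but is excluded under Table 1 (800 is below 1000).

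**4. What changes at score 12.** The text allows no exclusion on D-dimer. Table 1 allows it below max(500, 10 × age). Management differs for every patient with a D-dimer under that limit, at any age.

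**5. The benchmark for the secondary endpoint.** The article's limit reproduces: 1.82 + 0.00528 × 14 = 1.82 + 0.074 = 1.89%. The upper confidence limit of the 4PEPS false-negative rate is compared with this figure. The boundaries decide which patients count as ruled out by the strategy; they do not alter the limit through the formula.

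**The case against.** The strongest reply is that the Introduction is background. It cites Table 1 and the published derivation of the score, and Table 1 is the only complete statement of items, points and categories. The natural reading is then that the sentence paraphrases the table and gets the inequalities wrong. In practice, SPEED calculates the score and issues the recommendation, and nothing shows that the software carries two sets of boundaries. This has some force: the cross-reference hints that the table governs. It does not settle the matter, because the Introduction's set is just as complete and coherent. Section 6.2 gives no boundaries of its own, and the paper CRF offered alongside SPEED is not shown.

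A second reply concerns the false-negative endpoint. Section 3.2 does not restrict rule-out to D-dimer. If negative imaging after a non-excluding D-dimer also counts, many disputed patients stay in the denominator under either set. That stands as a limit on the effect, but it does not remove it: patients with positive imaging would leave the denominator, patients managed against the governing rule would be classified differently, and a PE missed in the disputed group would change the numerator.

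Third, at score 5 Table 1 is not more permissive at every age: the two limits coincide at 100, and above 100 Table 1 is the stricter. This is correct and clinically negligible.

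**Conclusion.** The concern holds. The article gives two incompatible sets of boundaries for the strategy under test, and they conflict at exactly two attainable scores, 5 and 12. Table 1 excludes PE more readily at 12 at every age, and at 5 for patients under 100. This rests only on the two sets as printed, on the whole-number points in Table 1, and on reading the Introduction's age-adjusted cut-off as the one in Table 1.

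The size in patients is unknown, because the article gives neither the distribution of scores nor that of D-dimer values at those scores. Only part of the patients at each score is affected: those in the D-dimer window at 5, and those below the age-adjusted limit at 12. No error in the sample size or in the primary analysis follows from it. It should be fixed because it leaves the intervention, one secondary safety endpoint and the per-protocol analysis open to two readings. The article does not show which set is right.

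**What to change.** Before the first inclusion, check the boundaries against the validated score and make the two places agree:

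- If Table 1 is right, the Introduction should read low 0 to 5, moderate 6 to 12, high above 12.
- If the Introduction is right, Table 1 should read low 0 to 4, moderate 5 to 11, high 12 or more.

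Either correction removes both conflicts. Then confirm that the SPEED algorithm, the paper CRF, the definition of PE ruled out by the 4PEPS strategy (sections 3.2 and 9.3) and the per-protocol definition (section 9.1) all use that set.

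The cost is negligible: one corrected sentence or table and a check of the coded cut-offs. The Abstract gives the trial status as not started. Once inclusion begins, a mismatch could mean reclassifying patients already managed under the wrong threshold.

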## 2. Study Design

We will test this study hypothesis in a prospective pragmatic cluster-randomized trial, with half of the centers in a control group where physicians will be free to do as they see fit but they will be given the recommendation to apply a validated strategy, and half of the centers will be in the interventional group where the physicians will be given the recommendation to apply the 4PEPS strategy [19,20]. 

## 3. Study Objectives and Endpoints

### 3.1. Primary Objective and Endpoints 

The primary objective is to demonstrate that the application of the 4PEPS strategy by the emergency physicians in comparison to current practices (i) does not increase the risk of serious events related to diagnostic strategies and (ii) significantly reduces the use of thoracic imaging. 

The primary safety endpoint will be the rate of serious events in the 90 days following inclusion:Serious adverse events related to diagnostic testing (leading to hospitalization or prolongation of hospitalization, permanent inability or incapacity, and death).Symptomatic thromboembolic events in patients not diagnosed with PE in the emergency department or new thromboembolic events in patients diagnosed with PE.Death related to PE (initial or recurrent PE).Major bleeding related to the anticoagulant treatment prescribed for pulmonary embolism according to ISTH criteria [21].

All events must be symptomatic, documented, and confirmed by the clinical adjudication committee blinded to the study group. For analysis of deaths in cases where an autopsy is not performed, a precise definition of the elements indicating that the death is possibly related to pulmonary embolism will be used according to recent ISTH proposals [22].

The primary efficacy endpoint will be the rate of thoracic imaging among all included patients with suspected PE. A relative reduction of at least 20% is expected.

The following thoracic examinations will be considered if they are performed at the request of the emergency physician in search of PE and this during the passage in the emergency department and/or within 72 h of inclusion:CTPA.Planar perfusion or perfusion–ventilation pulmonary scintigraphy.SPECT scintigraphy.

The examinations have to be mentioned in the patient’s record and be the subject of a report, with analysis of the file taken as proof of this. 

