## 5. Experimental Plan and Randomization

SPEED&PEPS will be an open-labelled cluster-randomized study, with 10 centers being allocated to the control group and 10 centers to the interventional group. Before randomization, participating centers will perform a preliminary assessment of the number of patients being investigated for suspected PE per month and of the rate of imaging test performed in patients suspected of PE in order to have an accurate idea of their baseline status [20]. These two criteria will be applied as stratification criteria during randomization to assure comparability between groups. 

SPEED&PEPS will be a pragmatic trial as confirmed by the PRECIS-2 rating of 42 out of 45 on the scale, with 0 corresponding to a fully explanatory study and 45 to a fully pragmatic study (cf. supplemental material) [24]. 

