## 7. Study Participant Follow-Up 

Data relating to care at the emergency department and the eventual subsequent hospitalization (characteristics, comorbidities, clinical and paraclinical data, confirmed diagnosis or diagnoses, possible adverse events, and treatment) will be compiled and entered into the eCRF. At discharge from the hospital, patients will be instructed to return to the ED or to contact their family physician in the event of any symptoms that may suggest a possible thromboembolic event or bleeding.

Patients and/or their relatives and family physician(s) will be contacted by phone and/or post or email at the end of the 3-month follow-up period. Using a standardized questionnaire, they will be asked about whether a thromboembolic event or bleeding has occurred; what examinations, consultations, or hospitalizations have taken place; and whether anticoagulant treatment has been introduced. Examination results (biological tests including D-dimer, ultrasonography, thoracic imaging…), hospital discharge summaries, and circumstances and causes of death, if any, will be collected. For each possible event during the follow-up, an adjudication file will be constituted, including reports of all relevant exams. All possible events will be adjudicated by the independent committee, blinded of randomization arm (control or interventional group). 

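### The primary imaging endpoint counts only scans that the emergency physician requests in search of PE, so scans within 72 h requested by others are scored as not done, while the objective and rationale concern thoracic imaging as such

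*Protocol article*

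**What the plan says.** All references are to the Protocol article. Section 3.1 states the second half of the primary objective as showing that 4PEPS, applied by emergency physicians, "significantly reduces the use of thoracic imaging". It names the endpoint broadly: "The primary efficacy endpoint will be the rate of thoracic imaging among all included patients with suspected PE". It then narrows what counts. CTPA, planar scintigraphy and SPECT are considered "if they are performed at the request of the emergency physician in search of PE". A time condition is added: the scan must fall in the emergency stay or in the first 72 h after inclusion. For proof, "The examinations have to be mentioned in the patient’s record and be the subject of a report".

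Sections 10 and 10.2 size the trial on the usage rate of thoracic imaging (45% in control, 36% in intervention) and do not repeat the requester or purpose condition. Section 12 justifies the trial by radiation exposure, time in the department and cost.

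On blinding, Section 5 says: "SPEED&PEPS will be an open-labelled cluster-randomized study, with 10 centers being allocated to the control group and 10 centers to the interventional group". Section 7 says of follow-up events: "All possible events will be adjudicated by the independent committee, blinded of randomization arm". The article states no such blinded step for classifying scans. Section 7 also provides for collecting "Data relating to care at the emergency department and the eventual subsequent hospitalization", together with thoracic imaging results at the end of follow-up.

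**The concern.** The conditions on requester, purpose and time are cumulative. The 72 h window extends when a scan may take place but not who may have asked for it. A CTPA ordered by the ward team the day after admission is therefore scored as no imaging, although the patient receives the radiation and the payer bears the cost.

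This would not matter if uncounted scans were equally frequent in the two arms. There is reason to think they may not be. The recommendation to use 4PEPS reaches emergency physicians in intervention centres only, and it is expected to leave more of their patients unscanned when they leave the department. Those patients can still be scanned by clinicians whom the intervention does not address. The stated purpose of a scan is also read from files written by staff who know the arm. If uncounted scans are more frequent in the intervention arm, the endpoint shows a larger fall in imaging than patients experienced, and the endpoint as defined cannot reveal this.

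**Working it through.** **1. The plan's own figure.** Inputs from Section 10.2: 45% against 36%, one-sided 5%, power 80%, ICC 0.05, 20 centres, total 2128. Under individual randomization these rates need 367 patients per arm. With 10 centres per arm and ICC 0.05, the effective size per arm stays below 10 / 0.05 = 200 however many patients are enrolled. So 2128 does not reproduce; it corresponds to an ICC of about 0.018. That is a separate matter and does not decide this point, but it is why results are shown below for both ICC values.

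**2. How the rule enters the comparison.** For each arm let T be the proportion scanned by anyone within 72 h, C the proportion counted, and U the proportion with uncounted scans only, so that T = C + U. Then

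counted difference = C(control) − C(intervention) = [T(control) − T(intervention)] + x, where x = U(intervention) − U(control).

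Only the net excess x distorts the comparison. If x = 0 there is no distortion; if x is negative the reduction is understated.

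**3. Size relative to the planned effect.** The planned effect is 45 − 36 = 9 points, so each point of x is 1/9 of it. If exactly 9 points are counted, the difference in total imaging is 9 − x:

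- x = 2: 7 points, or 7/45 = 15.6% relative, against a counted 20%
- x = 3: 6 points, or 13.3%
- x = 4.5: 4.5 points, or 10%

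**4. What x requires.** Under the planned rates, 55% of control and 64% of intervention patients have no counted scan. If the same share r of these patients is later scanned by someone else in both arms, then x = r × (64 − 55) = 9r points. A rule applied identically can therefore still give x above zero. But x = 2 needs r = 2/9 = 22%, and x = 4.5 needs r = 50%, unless the later-scan share itself differs by arm. The upper end is a demanding scenario.

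**5. Probability of a wrong claim about total imaging.** Inputs: 1280 per arm (Section 10.1), 128 per centre, ICC 0.05, one-sided 5%.

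- Design effect = 1 + (128 − 1) × 0.05 = 7.35
- Effective size = 1280 / 7.35 = 174.1 per arm
- SE at 45% in both arms = √(2 × 0.45 × 0.55 / 174.1) = 0.0533
- P(claim) = Φ(x / 0.0533 − 1.645), taking T equal in both arms

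With the ICC of 0.018 that 2128 implies, the design effect is 3.286, the effective size 389.5 and the SE 0.0357.

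| Net excess x (assumed) | ICC 0.05 | ICC 0.018 |
|---|---|---|
| 0 points | 5% | 5% |
| 2 points | 10% | 14% |
| 3 points | 14% | 21% |
| 4.5 points | 21% | 35% |

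These figures describe the limiting case in which every scan that emergency physicians avoid is replaced by another physician's scan. In that case the endpoint as defined has truly fallen, and the error lies in reading it as a fall in total imaging.

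**The case against.** The strongest reply is that the definition fits its target. The objective concerns a strategy applied by emergency physicians, the intervention addresses only them, and counting what they request in search of PE measures the behaviour to be changed while excluding unrelated imaging. The rule is explicit, fixed in advance and the same in both arms. This stands, and it is why the definition need not be replaced. It does not turn a count of one group's requests into the use of thoracic imaging on which the radiation and cost argument rests.

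A reader might infer that the bias can only favour 4PEPS, or that intervention physicians are told not to image. The documents support neither. Section 6.2 gives a recommendation to apply 4PEPS, and that strategy still calls for imaging in some patients. Section 6.1 recommends a validated strategy in control centres, so patients there are also ruled out without imaging and can also be scanned later. No passage gives a rate of scans ordered by others, or a difference by arm. An excess in the intervention arm is the likelier direction, not a documented one.

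The plan also has partial safeguards. Scans that the emergency physician requested but that took place after transfer are counted. A displaced scan that finds symptomatic PE may count as a safety event, and safety is tested first (Section 9.2). Hospital resource use is costed over 90 days (Section 8). These limit the harm, but none adds the uncounted scan to the imaging rate. Whether a scan took place is objective; within the record, mainly its purpose is open to judgement.

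Finally, a supporting analysis may exist in a fuller protocol or analysis plan that is not shown. The point therefore rests on the definition that the article states, not on the absence of an analysis.

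**Conclusion.** The gap between endpoint and claim is certain from the text: an uncounted scan within 72 h is scored as no imaging, while the objective, sample size and rationale refer to thoracic imaging without that limit. That this distorts the comparison between arms is plausible but not shown. The 2 to 4.5 points are an assumption chosen for illustration, and zero is also possible. The rise from 5% to about 10% to 21% at ICC 0.05 depends on that assumption and on no true fall in total imaging, so it must not be read as this trial's error rate. If emergency-requested imaging falls and only some of it is replaced, the consequence is an overstated reduction rather than a false one. The matter is worth settling before the data are seen because the remedy is cheap.

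**What to change.** Keep the primary definition and the primary decision rule. Pre-specify one supporting analysis, using the same mixed-effects logistic model, that counts every CTPA or lung scintigraphy within 72 h of inclusion whatever the requester or stated indication, and report it beside the primary result. State in advance that, if it does not show a similar reduction, the primary conclusion will be worded as a reduction in imaging requested by emergency physicians. The supporting analysis governs the wording of the conclusion; it is not a second condition for statistical success.

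The cost is a sentence or two and one more model run, on data that Section 7 already provides for; the team should confirm that the date and type of each scan are recorded. The small downside is that imaging unrelated to PE adds some noise to the supporting analysis.
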